#### **9.5.6.2. Impact on Work and Daily Activities**

Impairment associated with HCV infection or its treatment in terms of missed time from work, reduced effectiveness while at work, and impairment in daily activities will be assessed at baseline and at study visits throughout treatment and follow-up as specified in the Time and Events Schedule. The WPAI:Hepatitis C questionnaire (see Attachment 4) includes 6 questions that have been successfully used to compare work productivity and daily activity impairment in patients with chronic HCV infection who received PegIFN $\alpha$ -2a versus the combination of PegIFN $\alpha$ -2b and RBV. Two primary scores are provided in the standard scoring of the WPAI:Hepatitis C: a productivity score (combining missed time and reduced effectiveness at work for subjects who are employed), and a daily activity impairment score for all subjects. In addition, the impact of HCV and its treatment can be examined in terms of missed time from work and reduced effectiveness while at work as separate outcomes.

### **9.5.6.3. Health Status and Quality of Life**

Impact of treatment and of HCV infection on health status and quality of life will be assessed using the EQ5D. Subjects will self-administer the EQ5D at baseline and during study visits throughout treatment and follow-up as specified in the Time and Events Schedule. The EQ-5D questionnaire (see Attachment 5) is an instrument designed to assess overall health status using 5 health dimension scores (mobility, self-care, usual activities, pain/discomfort, anxiety/depression) and a "thermometer" visual analog scale (VAS) ranging from 0 (worst imaginable health state) to 100 (best imaginable health state). It takes approximately 8 minutes to complete and was designed for self-completion by respondents. The EQ-5D questionnaire is commonly used as a brief, generic HRQoL assessment and to incorporate patient preference values into health economic evaluations.

Scores for the EQ5D include the Valuation Index, the visual analog scale (VAS) and 5 health dimension scores (also known as the EQ5D Descriptive System scores).

### **9.5.6.4. Fatigue**

The FSS will be completed by the subject at time points indicated in the Time and Events Schedule. The FSS (Attachment 6) is a self-administered questionnaire with 9 items developed to assess disabling fatigue that has been used extensively in studies of chronic HCV infection. Item responses are measured on a 7-point Likert scale ranging from strongly disagree (1 point) to strongly agree (7 points). The 9 items are averaged to produce a total score; a lower total score indicates less effect of fatigue on everyday life. The FSS has demonstrated good internal consistency, test-retest reliability and construct validity in patients with chronic HCV infection. The recall period of the FSS used in this study is 2 weeks (the past 14 days).

For further guidance, see also Section 9.1.3.

### **9.5.6.5. Depressive Symptoms**

The Center for Epidemiologic Studies Depression Scale (CES-D) will be completed by the subject at time points indicated in the Time and Events Schedule. The CES-D (Attachment 7) is a self-administered, 20-item questionnaire developed based upon extensive in-depth interviews with patients. The CES-D has been used extensively to measure the impact of HCV treatment on depressive symptom severity. A total score for the CES-D is available and is based upon the assessment of the dimensions of depressed affect, positive affect, somatic impact and interpersonal impact of depression. The total score ranges from 0 to 60, with lower scores indicating a lower depressive symptom severity during the past week. The CES-D has demonstrated good internal consistency, test-retest reliability and construct validity in a sample of patients with chronic HCV infection.

For further guidance, see also Section 9.1.3.

### 9.5.7. Specific Toxicities

The safety monitoring and toxicity management plan described below takes into account AEs based on the clinical safety data of TMC435 and toxicities reported with PegIFN $\alpha$ -2a and RBV. For guidance on discontinuation of TMC435 during the treatment period, refer to Section 6.

Note that the following definitions apply:

Investigational medication: TMC435

Study medication: Before Week 12 of the study:

TMC435 plus PegIFN $\alpha$ -2a and RBV triple therapy

After Week 12 of the study:

PegIFN $\alpha$ -2a and RBV

#### 9.5.7.1. Rash

**Subjects should be informed that they should contact their study doctor immediately if they notice any rash.**

The rash event should be captured in the Adverse Event section of the eCRF.

Monitoring of the evolution of rash will be performed based on the grade (severity) of the rash (see Attachment 8). At the investigator's discretion, additional visits and assessments can be performed.

When safety blood samples are drawn, these should be processed by the local laboratory. The following parameters will need to be tested: AST, ALT, sedimentation rate, and complete blood cell count (including hemoglobin, hematocrit, RBC count, WBC count, platelet count, neutrophils, lymphocytes, monocytes, eosinophils, basophils and creatinine). The values of the local laboratory assessments need to be transcribed in the eCRF by the site staff.

The subject may be treated symptomatically until the rash resolves. Oral antihistamines (e.g., cetirizine, levocetirizine) and/or topical corticosteroids may provide symptomatic relief but effectiveness of these measures has not been established. If systemic corticosteroids for longer than 24h are required for treatment of rash, the investigational medication needs to be permanently discontinued. If the rash is considered to be most likely due to concomitant illness or nonstudy medication, standard management, including discontinuation of the likely causative agent, should be undertaken.

Dermatologist fees for evaluating subjects who experience a rash will be reimbursed by the sponsor.

The following grades are based on the WHO grading table (see Attachment 2), with adaptations made by the sponsor.

**Grade 1 Rash (with or without pruritus)**

A grade 1 rash is defined as **erythema**.

- Subjects may continue the intake of study medication (at the investigator's discretion). If only TMC435 is discontinued, PegIFN $\alpha$ -2a/RBV can be continued at the investigator's discretion.
- An unscheduled visit including a safety laboratory evaluation should be performed as soon as possible after the subject contacts the investigator to report the AE.
- Assessment of safety blood samples by the local laboratory is required. The values of the local laboratory assessments need to be transcribed in the eCRF by the site staff.

Unscheduled visits will also be performed after the initial rash assessment at the investigator's discretion for appropriate follow-up until resolution of the rash. At these visits, safety blood samples can be taken at the investigator's discretion. For these and all subsequent local laboratory blood sample assessments, the values of the assessments need to be transcribed in the eCRF by the site staff.

**The subject should be advised to contact the investigator immediately if there is any worsening of the rash, if any systemic signs or symptoms appear, or if mucosal involvement develops.**

In case the rash evolves from a grade 1 to a higher grade, management of the rash should follow the guidelines indicated for grade 2 or grade 3-4 rash, respectively.

**Grade 2 Rash (with or without pruritus)**

A grade 2 rash is defined as **diffuse, maculopapular rash, OR dry desquamation**.

- Subjects may continue the intake of study medication (at the investigator's discretion). If only TMC435 is discontinued, PegIFN $\alpha$ -2a/RBV can be continued at the investigator's discretion.
- An unscheduled visit including a safety laboratory evaluation should be performed as soon as possible after the subject contacts the investigator to report the AE.
- Assessment of safety blood samples by the local laboratory is required. The values of the local laboratory assessments need to be transcribed in the eCRF by the site staff.
- Referral to a dermatologist is optional but, when done, should occur preferably within 24 hours after the onset of the rash. A copy of the dermatologist's report should be made anonymous and will be collected by the monitor.

Unscheduled visits will also be performed after the initial rash assessment at the investigator's discretion for appropriate follow-up until resolution of the rash. At these visits, safety blood samples must be taken. For these and all subsequent local laboratory blood sample assessments, the values of the assessments need to be transcribed in the eCRF by the site staff.

**The subject should be advised to contact the investigator immediately if there is any worsening of the rash, if any systemic signs or symptoms appear, or if mucosal involvement develops.**

In case the rash evolves from a grade 2 to a grade 3-4 rash, management of the rash should follow the guidelines specified for grade 3-4 rash.

### **Grade 3 or Grade 4 Rash**

A grade 3 rash is defined as a rash associated with:

- **vesiculation, moist desquamation, or ulceration OR**
- **Any cutaneous event with 1 of the following:**
  - **elevations in AST/ALT more than 2 x baseline value;**
  - **fever > 38°C or 100°F;**
  - **eosinophils > 1000/mm^3;**
  - **serum sickness-like reaction.**

A grade 4 rash is defined as:

- **exfoliative dermatitis OR**
- **mucous membrane involvement OR**
- **erythema multiforme OR**
- **Stevens-Johnson Syndrome (SJS) OR**
- **necrosis requiring surgery.**

Subjects will permanently discontinue the intake of study medication. No rechallenge is allowed.

An unscheduled visit including a safety laboratory evaluation should be performed as soon as possible after the subject contacts the investigator to report the AE.

Assessment of safety blood samples by the local laboratory is required on the day of initial rash evaluation and the day thereafter (Days 0 and 1). The values of the local laboratory assessments need to be transcribed in the eCRF by the site staff.

Referral to a dermatologist is required, preferably within 24 hours after the onset of the rash. A copy of the dermatologist's report should be made anonymous and will be collected by the monitor.

A biopsy is to be performed at the discretion of the dermatologist for grade 3 rash and should be performed in case of a grade 4 rash. A copy of the dermatologist's report, and the biopsy if performed, should be made anonymous and will be collected by the monitor.

Appropriate management should be undertaken and subjects should be followed until resolution of the rash or until clinical stability is reached.

A complete summary of the guidelines for rash management is given in Attachment 8.

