### **10.2. Discontinuation of Study Treatment**

If a subject's study treatment must be discontinued before the end of the treatment regimen, this will not result in automatic withdrawal of the subject from the study.

At the discretion of the investigator, all study medication (TMC435, PegIFN $\alpha$ -2a and RBV) may be discontinued for any of the following reasons:

- An SAE occurs.
- The subject fails to comply with the protocol or study staff requirements.

All study medication (TMC435, PegIFN $\alpha$ -2a and RBV) must be discontinued for any of the following reasons:

- withdrawal of consent.
- The subject meets a virologic stopping criterion at Week 4 or 12 or experiences viral breakthrough at any time point during treatment (see Section 6.3).
- The investigator believes that for safety reasons (e.g., AE) it is in the best interest of the subject to discontinue study treatment.
- The subject becomes pregnant.
- A subject fails to comply with the contraception requirements (in female subjects; refer to Section 4.3).
- The subject experiences a grade 3 or 4 rash/allergic reaction (see Sections 9.5.7.1 and 9.5.7.2).
- The subject experiences severe worsening of hepatic disease (see Section 9.5.7.4).

Subjects must discontinue investigational medication (TMC435) and may continue PegIFN $\alpha$ -2a and/or RBV alone if:

- They require treatment with one of the medications included in the list of disallowed concomitant medications (see Section 8).

- The subject experiences grade 4 ALT/AST elevations  $> 2 \times$  baseline value and concurrent grade 4 bilirubin values and the ALT/AST and bilirubin values continue to meet grade 4 criteria at re-testing performed 72 hours after receipt of the results (see Section 9.5.7.3).
- The subject experiences a grade 3 or 4 AE (other than the rash/allergic reaction AE mentioned above) or confirmed grade 3 or 4 laboratory abnormality (other than grade 3 isolated increases in AST/ALT or bilirubin) considered to be at least possibly related to TMC435 (2 consecutive measurements no more than 72 hours after receipt of first results). This excludes AEs or laboratory abnormalities that are not considered to be at least possibly related to TMC435. Subjects who have known Gilbert's disease and experience isolated grade 4 elevated indirect bilirubin can continue the investigational medication at the investigator's discretion.

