| Muscle Strength                                  | subjective weakness no objective symptoms/ signs                               | mild objective signs/symptoms no decrease in function                              | objective weakness function limited                                                      | paralysis                                                          |

| Item                    | Grade 1                        | Grade 2                                        | Grade 3                                         | Grade 4                                                                                                                                |
|-------------------------|--------------------------------|------------------------------------------------|-------------------------------------------------|----------------------------------------------------------------------------------------------------------------------------------------|
| Other Parameters |                                |                                                |                                                 |                                                                                                                                        |
| Fever: oral, >12 hours  | 37.7-38.5 °C or 100.0-101.5 °F | 38.6-39.5 °C or 101.6-102.9 °F                 | 39.6-40.5 °C or 103-105 °F                      | >40 °C or >105 °F                                                                                                                      |
| Headache                | mild, no Rx therapy            | transient, moderate; Rx required               | severe; responds to initial narcotic therapy    | intractable; required repeated narcotic therapy                                                                                        |
| Fatigue                 | no decrease in ADL             | normal activity decreased 25-50%               | normal activity decreased >50% can't work       | unable to care for self                                                                                                                |
| Allergic Reaction       | pruritus without rash          | localized urticaria                            | generalized urticaria; angioedema               | anaphylaxis                                                                                                                            |

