| Local Reaction          | tenderness or erythema         | induration <10 cm or phlebitis or inflammation | induration >10 cm or ulceration                 | necrosis                                                                                                                               |
| Mucocutaneous           | erythema; pruritus             | diffuse, maculo papular rash, dry desquamation | vesiculation, moist desquamation, or ulceration | exfoliative dermatitis, mucous membrane involvement or erythema, multiforme or suspected Stevens-Johnson or necrosis requiring surgery |

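### The Grade 3 rash fever trigger pairs 38°C with 100°F, but 38°C is 100.4°F, so a mandatory stop rule carries two limits 0.22°C apart

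*Protocol*

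**What the plan says.** Section 9.5.7.1 (Rash) grades rash from 1 to 4 and ties each grade to an action. The grades are the sponsor's own version of a standard table: "The following grades are based on the WHO grading table (see Attachment 2), with adaptations made by the sponsor".

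One way to reach Grade 3 is any cutaneous event together with one of four findings: an AST/ALT rise above twice baseline, eosinophilia, a serum sickness-like reaction, or "fever > 38°C or 100°F".

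The action for Grade 3 or 4 is fixed: "Subjects will permanently discontinue the intake of study medication. No rechallenge is allowed". Section 10.2 lists "The subject experiences a grade 3 or 4 rash/allergic reaction" among the reasons for which all study medication must be stopped, and Section 1.5.5 and Attachment 8 repeat the mandatory stop. Section 9.5.7 defines study medication by phase: up to Week 12 it is TMC435, PegIFNα-2a and RBV together, and afterwards PegIFNα-2a and RBV.

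For Grade 1 the rule is permissive: "Subjects may continue the intake of study medication (at the investigator's discretion"). Grade 2 has the same rule.

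**The concern.** A temperature limit given in two units should be one limit. Here the two figures differ, and they sit at the boundary between a compulsory permanent stop and a decision left to the investigator. This is a multicenter, international study. A site reading in Fahrenheit and a site reading in Celsius could take the same patient at the same temperature and reach different obligations, each following the text as printed. What is at stake is consistent application of a safety stop rule, and for the individual subject the possible loss of all three drugs during triple therapy.

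**Working it through.** **Inputs.** Both limits, 38°C and 100°F, come from the Grade 3 definition in Section 9.5.7.1. I take the greater-than sign to apply to both.

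**Conversion.** F = C × 1.8 + 32 and C = (F − 32) / 1.8.

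- 38°C: 38 × 1.8 + 32 = 100.4°F. The printed 100°F is not reproduced, except by rounding to the whole degree.
- 100°F: (100 − 32) / 1.8 = 37.78°C.
- Gap: 38.00 − 37.78 = 0.22°C, or 100.4 − 100 = 0.4°F.

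**Example.** A reading of 100.2°F exceeds 100°F. The same temperature is (100.2 − 32) / 1.8 = 37.89°C, which does not exceed 38°C.

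**What each reading requires.** Take a cutaneous event otherwise Grade 1 or 2, no other Grade 3 or 4 feature, and a temperature above 37.78°C and up to 38.0°C.

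| Reading of the text | Effective limit | Consequence in the band |
|---|---|---|
| The word *or* taken literally (either limit suffices) | > 37.78°C at every site | Permanent stop required |
| Unit equivalents, site uses Fahrenheit | > 37.78°C | Permanent stop required |
| Unit equivalents, site uses Celsius | > 38.0°C | Investigator's discretion |

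**Does the rest of the protocol settle it?** No.

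- The Grade 3 mucocutaneous entry in Attachment 2 reads "vesiculation, moist desquamation, or ulceration". It has no fever item, so the source table cannot supply the limit.
- Attachment 8 repeats the stop without a temperature.
- The separate fever row in Attachment 2 starts Grade 1 at "37.7-38.5 °C or 100.0-101.5 °F", which sets 100.0°F beside 37.7°C rather than 38°C. Its lower pair is 37.7 × 1.8 + 32 = 99.86°F against the printed 100.0°F, a difference of 0.14°F. The row is loose elsewhere, however: Grade 4 prints 40°C with 105°F, although 40 × 1.8 + 32 = 104°F. It cannot serve as a benchmark for exact pairing.
- The storage temperatures in Section 14.4 are converted exactly, with a decimal where one is needed: 2 × 1.8 + 32 = 35.6°F and 8 × 1.8 + 32 = 46.4°F, as printed.

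**The case against.** The strongest reply is that this is one threshold with a rounded gloss. Both values are whole degrees, 100.4 rounds to 100, and where the protocol gives two units it puts Celsius first, so 38°C is the lead value. Rounding may well explain how 100°F got there. It does not remove the difference, because a cut-off is applied as printed, and Section 14.4 shows that whole-degree rounding is not the protocol's general practice.

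A second reply is that a literal *or* gives a single answer everywhere: anything above 100°F qualifies. That is correct, and inconsistency between sites then arises only if sites treat the figures as equivalents. But on the literal reading the 38°C figure does no work, and a site that measures in Celsius and relies on it would miss a required stop.

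Third, the Fahrenheit figure is the lower one, so applying it means stopping earlier. The investigator may in any case stop at a lower grade, and must stop if safety requires it. This stands: stopping a subject in the band complies with either reading. What remains unclear is whether stopping is compulsory, and Grades 1 and 2 deliberately leave that open.

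Fourth, the fever item fixes no route, device or duration of measurement, and scheduled vital signs cover blood pressure and pulse only, so 0.22°C is finer than the protocol controls. This also stands as a limit on practical importance, but it is no reason to print two different limits.

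Finally, no affected subject can be shown. Section 1.2 reports rash of any type in 23.2% and influenza-like illness in 26.0% of TMC435-treated subjects in the pooled Phase 3 studies. Low-grade fever alongside a rash is therefore plausible, but these rates say nothing about how often the two coincide within this band.

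**Conclusion.** The point holds. The Grade 3 rash definition states two temperature limits that are 0.22°C (0.4°F) apart, inside a rule that makes permanent discontinuation mandatory, and the protocol does not say which applies.

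The severity is minor. The discrepancy matters only for a subject in the narrow band with a cutaneous event and no other Grade 3 or 4 feature. Few subjects are likely to meet that description, and their number cannot be estimated from the protocol. The primary test, sample size, power and alpha are untouched. The conclusion rests on exact unit conversion and on the greater-than sign covering both figures.

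**What to change.** State a single limit in Section 9.5.7.1. If 38°C was intended, write > 38.0°C (100.4°F). If the lower value was intended, write > 37.8°C (100°F). The sponsor should decide which and tell the sites.

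The cost is one line of wording, in a clarification letter or the next amendment. Attachment 8 and Section 10.2 need no change because neither gives a temperature. Visits, data collection and analysis stay as they are.

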#### **9.5.7.2. Acute Systemic Allergic Reaction**

Oral antihistamines (e.g., cetirizine, levocetirizine) and/or topical corticosteroids may provide symptomatic relief but effectiveness of these measures has not been established. If systemic corticosteroids for longer than 24h are required for treatment of acute systemic allergic reaction, the investigational medication needs to be permanently discontinued.

#### **Grade 1 (Pruritus Suggestive of an Allergic Reaction Without Rash)**

Subjects may continue the intake of investigational medication or have their investigational medication discontinued at the investigator's discretion. Subjects may continue treatment with PegIFN $\alpha$ -2a or RBV at the investigator's discretion. Close clinical follow-up is recommended to monitor for any progression of the AE. Subjects should be advised to contact the investigator immediately if there is any worsening of symptoms.

